#### Secondary outcomes

Secondary outcomes will include whole-brain and hippocampal volume, evaluated using MRI; cognitive function, assessed using verbal fluency tests (VFTs) [31] and tablet versions of the trail-making test (TMT) [27] and symbol digit substitution test (SDST) [27]; brain-derived neurotrophic factor (BDNF) serum levels; and health-related quality of life (QOL).

Whole-brain and hippocampal volume will be determined using a 3-T system (TM Trio, Siemens, Germany). Three-dimensional volumetric acquisition of a T1-weighted gradient echo sequence will be performed to produce a gapless series of thin sagittal sections using a magnetization preparation rapid-acquisition gradient-echo sequence (inversion time [TI] 800 ms; repetition time [TR] 1800 ms; echo time [TE] 1.98 ms; and 1.1 mm slice thickness). Axial T2-weighted spin-echo images (TR 4200 ms; TE 89.0 ms; and 5.0 mm slice thickness) and axial fluid-attenuated inversion-recovery images (TI 2500 ms; TR 9000 ms; TE 100 ms; 5 mm slice thickness) will then be obtained for diagnosis.

Verbal fluency will be assessed according to the number of words generated across 60-second trials [32]. Both the letter VFT (which assesses phonemic verbal fluency) and the animal naming test (which assesses semantic verbal fluency) will be performed. In the letter VFT, participants will be instructed to retrieve as many words (excluding proper names) as possible within a 60-second period, beginning with the Japanese syllabic characters (hiragana) “Shi,” “I,” and “Re” [33]. The total number of words generated for all three letters will be used as a measure of performance. In the animal naming test, participants will be instructed to generate a list of animal names within 60 seconds [31]. The tablet version of the TMT, consisting of parts A and B, will be used to determine attention and executive function [27]. In the tablet version of the TMT-A, participants are required to touch target numbers (1–15), which are presented randomly on the panel, in consecutive order as rapidly as possible. In the tablet version of the TMT-B, participants touch target numbers or letters, alternating between consecutive numbers and letters (Japanese Kana characters). We will record the time (in seconds) taken to complete each task; a shorter time represents superior performance. In the tablet version of the SDST, nine pairs of numbers and symbols are presented at the top of the display, and a target symbol is shown in the center of the display. Participants then choose a number that corresponds to a target symbol, which is presented at the bottom of the display, as rapidly as possible. The number of correct numbers chosen within 90 seconds constitutes the score. One point is awarded for each number that is chosen correctly within the time limit. The tablet versions of the TMT and SDST have demonstrated reliability and validity in a sample of community-dwelling older adults [27].

Serum BDNF levels will be measured using the Quantikine Human Kit (R & D Systems, Inc. Minneapolis, MN, USA) and used as a biomarker [12].

Health-related QOL will be assessed using the Short-Form Health Survey-12, a standardized instrument with established psychometric validity, which measures eight health domains: physical functioning, role limitations due to physical health, bodily pain, general health, vitality (energy/fatigue), social functioning, role limitations due to emotional health, and mental health (psychological distress and wellbeing) [34].

#### Other outcomes

Other outcomes will include physical performance tests such as handgrip strength, walking speed, and the two-minute walking test [35]; social network, assessed using the abbreviated version of the Lubben Social Network Scale (LSNS-6) [36]; Life-Space Assessment (LSA) [37]; subjective sleep quality, assessed using the Pittsburgh Sleep Quality Index [38]; and daily physical activity level, assessed using a triaxial accelerometer [39]. We will monitor adherence to the intervention programs and record adverse events.

Physical performance tests will include handgrip strength to measure muscle strength, normal and maximum walking speed to measure general gait ability, and the two-minute walking test to assess exercise tolerance. Handgrip strength and walking speed are simple, easy to implement in community settings, and strong predictors of health outcomes [40]. In the two-minute walking test, participants will be asked to walk, covering as much ground as possible in a demarcated area within 2 minutes. The distance walked within 2 minutes will be measured [35].

Social network will be measured using the LSNS-6, which is a six-item scale (simple sum scoring with a range of 0–30) consisting of three items that evaluate kinship ties and three items that evaluate non-kin ties [36]. Life-space mobility will be measured via the LSA, which is used to obtain a score based on the reported distance travelled during the 4 weeks preceding assessment. Scores range from 0 (“totally roombound”) to 120 (“travelled out of town every day without assistance”), with lower scores reflecting lower life-space mobility [37, 41]. Sleep quality will be evaluated using the Pittsburgh Sleep Quality Index, which consists of 19 items that produce a global sleep quality score and scores for the following seven components: sleep quality, latency, duration, disturbance, habitual sleep efficiency, use of soporific medication, and daytime dysfunction. The sum of these seven component scores yields one global score for subjective sleep quality (range 0–21), with higher scores reflecting poorer subjective sleep quality [42]. Daily physical activity level, including duration of light, moderate, and total physical activity, and the numbers of steps taken during the 2-week periods subsequent to pre-intervention and post-intervention assessments, will be measured using a triaxial accelerometer [39].

### Statistical analyses

Statistical analyses will be conducted to assess the effects of interventions according to the intention-to-treat principle, which states that data for all individuals should be analyzed according to their group allocation, regardless of compliance. Data will be entered according to a multiple imputation method. Between-group differences in primary outcomes subsequent to intervention will be compared using multiple linear regression analysis. Baseline scores, experimental groups, and characteristics (e.g., age, sex, diagnoses, and medical conditions) will be included in the models as covariates. If the effects of the intervention are significant, two planned simple contrasts will be performed to assess differences between the EI and control groups and the HI and control groups. Contrasts will also be performed within each intervention group to determine whether intervention benefits are observed for the primary outcomes. The analysis performed for the primary outcomes will also be performed for the secondary and other outcome measures.

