## Methods/Design

### Study design

The proposed study is a randomized single-blind controlled community-based trial with a parallel design and a 1:1:1 allocation ratio. The study design is shown in Fig. 1. We will recruit 90 community-dwelling adults aged 65 years or older with memory problems and depressive symptoms. Informed consent will be obtained from all participants prior to their inclusion in the study. The study protocol was approved by the Ethics Committee of the National Center for Geriatrics and Gerontology (#839).

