### Sample size

The required sample size for this study was calculated using predictions of 6-month changes in GDS-15 results. Based on the results of our previous work, conducted in the same town, we predict that a change of 1.5 GDS-15 points would indicate differences and assume that the SDs for the GSD-15 would be 2.5 in our sample. Assuming a non-consent and dropout rate of 20–30 %, 30 participants are required per group. The study design necessitates power of at least 80 % and an α level of <.05 to assess the effects of the interventions.

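### The EI–control and HI–control contrasts, which are the trial's question, are performed only after a significant overall effect; both should always be reported, and the power figure should name the test it describes

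*Protocol article*

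**What the plan says.** The Statistical analyses section compares the groups on the primary outcomes by multiple linear regression, with baseline score, group and participant characteristics in the model. It then sets a condition: "If the effects of the intervention are significant, two planned simple contrasts will be performed to assess differences between the EI and control groups". HI against control is treated in the same way. The test that decides whether the effects are significant is not named. The same analysis is to be applied to the secondary and other outcomes.

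The Sample size section bases the trial on the 6-month change in GDS-15: "we predict that a change of 1.5 GDS-15 points would indicate differences and assume that the SDs for the GSD-15 would be 2.5". It continues: "Assuming a non-consent and dropout rate of 20–30 %, 30 participants are required per group", and "The study design necessitates power of at least 80 % and an α level of <.05 to assess the effects of the interventions". It mentions no overall test, no second comparison and no condition on the contrasts.

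**The concern.** The trial asks whether each programme is better than the educational control. The two contrasts answer that, yet the written rule performs them only after another test has succeeded. Three consequences follow.

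- When the overall test fails, the rule as written yields no estimate or interval for either programme, although the Discussion promises conclusions on clinical importance as well as efficacy.
- When it succeeds, the reported estimates have been selected on significance, so a real effect tends to look larger than it is.
- A programme succeeds only if both the overall test and its own contrast are significant. One difference, one SD and 5 % alpha are the inputs of a single comparison, so the stated 80 % is not the power of the written rule.

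**Working it through.** **Inputs.** From Sample size: difference 1.5, SD 2.5 (not said to be of scores or of changes), alpha .05, 30 per group, 20–30 % non-consent and dropout. From Study design: "parallel design and a 1:1:1 allocation ratio". Assumed: two-sided tests, equal variances, normal outcomes and no covariate gain. If all the loss falls after randomisation, 30 × 0.8 = 24 or 30 × 0.7 = 21 per group are analysable. The HI effect is taken as 1.5 or 0; the value 0.75 is an illustration that is not in the protocol.

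**The plan's own figure.** For one two-group comparison, n = 2(1.96 + 0.84)² × 2.5² / 1.5² ≈ 43.6, so 44 per group (45 with the t distribution). Allowing for loss gives 44/0.8 = 55 to 44/0.7 ≈ 63. The overall three-group test needs about 42 before loss when HI is 0 or 1.5. Neither gives 30. A one-group change calculation does (24/0.8 = 30), but it is not the planned comparison. A baseline-adjusted two-group calculation reaches 30 only with an unstated correlation of about 0.6–0.7.

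**Chance that the gate opens.** The noncentrality of the overall F test is λ = n Σ(μ − μ̄)² / SD². With control, EI and HI means of 0, 1.5 and 1.5, the mean is 1.0 and the sum of squares is 1 + 0.25 + 0.25 = 1.5. At 30 per group λ = 30 × 1.5 / 6.25 = 7.2, and F on 2 and 87 df passes with probability 0.65. The contrasts are therefore not performed in 35 % of trials. At 24 and 21 per group the figures are 46 % and 51 %.

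**Power for EI–control.** The single contrast has noncentrality 1.5 / (2.5 × √(2/30)) = 2.32, which gives 63 %. The gated figures come from simulation (overall F test at 5 %, then a pooled-variance t contrast at two-sided 5 %), with step-down Dunnett for comparison.

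| n per group | HI effect | Single contrast | Gated | Step-down Dunnett | Mean EI estimate after passed gate (true 1.5) |
|---|---|---|---|---|---|
| 30 | 1.5 | 63 % | 56 % | 58 % | 1.80 |
| 30 | 0.75 | 63 % | 50 % | 54 % | 1.96 |
| 30 | 0 | 63 % | 56 % | 53 % | 1.80 |
| 24 | 1.5 | 54 % | 45–46 % | 48 % | 1.92 |
| 21 | 1.5 | 48 % | 40 % | 42 % | 2.00 |
| 45 | 1.5 | 81 % | 76 % | 78 % | 1.63 |

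**What the gate itself blocks.** With both programmes working, the EI contrast is significant but blocked in 7.2 % of trials at 30 per group and 8.2–8.5 % at 24–21. The rest of the 35–51 % is low power.

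**Error rates.** If neither programme works, the chance of any false contrast is 4.2 % gated, 5.0 % with step-down Dunnett and 9.0 % for two unadjusted contrasts.

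**Null effects.** With EI 1.5 and HI 0, the HI estimate after a passed gate averages 0.00.

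**Baseline adjustment.** The residual SD is 2.5 × √(1 − ρ²): 2.17 at ρ = 0.5 and 1.79 at ρ = 0.7. At 21–24 per group with both programmes working, the gate then stays closed in 15–39 % of trials, and gated power is 52–78 %.

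**The case against.** The strongest reply is that an overall test followed by pairwise contrasts is Fisher's protected LSD, which controls familywise error with three groups. That stands, and it limits the point. A reader might infer from the fall from 63 % to 56 % (or 50 %) that the gate wastes 7–13 points of power. The documents do not support that: the 63 % belongs to an unadjusted contrast, two of which carry about 9 % familywise error, and the 13 rests on the illustrative HI effect of 0.75. Against step-down Dunnett the gate runs from about 3 points better (other programme inert) to about 4 points worse (other programme half as effective). At 45 per group neither procedure reaches 80 %.

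A reader might also infer that every reported effect would be too large. That is wrong, since a null effect is not inflated. Nor is the gate the main source of inflation: reporting only significant ungated contrasts gives a mean of 1.88 at 30 per group.

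Nor should the 35–51 % be charged to the gate, because the overall test at 30 per group passes slightly more often (65 %) than a single contrast is significant (63 %). The 24 and 21 cases also put all the loss after randomisation, whereas the protocol combines non-consent with dropout and plans multiple imputation.

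Finally, the overall test is inferred, the regression would yield group estimates anyway, and reporting detail may sit in a fuller document. This softens the point without removing it: the article does not leave the matter open, but states a condition for performing the contrasts.

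**Conclusion.** The point holds in limited form. As written, the rule makes the trial's own comparisons depend on a preliminary test that would fail in about 35 % of trials at 30 per group with both programmes working (46–51 % at 24–21). Where estimates appear only after a passed gate, a true 1.5 averages 1.80 at 30 per group, or 1.96 if the other programme gives half the effect. The stated 80 % describes neither the written rule (about 56 %) nor a single contrast (63 %) at the sponsor's inputs.

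The gate is not invalid, and replacing it is not required. The figures rest on two-sided 5 %, equal variances, no covariate gain and reading the condition as an overall three-group test. A strong baseline correlation would raise power and reduce the selection, but the protocol states none.

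**What to change.** **Statistical analyses.** State that EI–control and HI–control will be estimated from the regression model and reported with 95 % confidence intervals whatever the overall result. Name the overall test. It may stay as the familywise gate for claiming that a contrast is significant. Step-down Dunnett or Holm is an alternative, not a correction. At 30 per group, step-down Dunnett gains about 2 points of power over the gate if both programmes work and about 4 if one works half as well, and loses about 3 if one is inert.

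**Sample size.** State which test the power figure refers to, and restate the figure for that test, with any baseline correlation and the post-randomisation loss assumed.

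**Cost.** Wording and one recalculation, with no extra participants or data for the reporting change. Always reporting both estimates and intervals has no statistical downside. The restated power may fall below 80 %, which the sponsor would then have to acknowledge. The Trial status section reports enrolment open with 29 recruited, so at that stage the change could be made before outcomes are analysed.

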### Study population

The study population will include community-dwelling older adults with mild memory decline and depressive symptoms. Participants will be required to meet the following inclusion criteria: (1) independent adults aged 65 years or older living within the community; (2) memory problems (subjective memory complaints or objective mild memory decline indicated via an age-adjusted word list memory score at least 1.0 SD below the reference threshold); and (3) presence of depressive symptoms (Geriatric Depression Scale-15 [GDS-15] score of ≥5) [24]. Participants will be excluded if they meet the following exclusion criteria: (1) support or care certified by the Japanese public long-term care insurance system; (2) dementia diagnosis or Mini-Mental State Examination score of ≤18; (3) a history of major psychiatric illness (e.g., bipolar disorder) or other serious neurological or musculoskeletal diagnoses; (4) disability in basic activities of daily living; (5) incapable of undertaking cognitive performance tests; (6) physical exercise contraindication; and (7) use of walking aids in daily life. Participants will also be excluded if they cannot sign the informed consent form.

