#### Primary outcomes

Primary outcomes will include a reduction in depressive symptoms, based on changes in GDS-15 scores, and an improvement in memory performance, assessed via word list memory [27] and the Logical Memory subtests of the Wechsler Memory Scale-Revised (WMS-R) [28]. The GDS-15 consists of 15 items. A score of 5 or higher will be used to identify clinical depressive symptoms [29, 30].

The word list memory tasks will involve immediate recognition and delayed recall of a 10-word target list [27]. Participants are instructed to memorize 10 words, which are presented on a tablet personal computer. Each of the 10 target words is presented for 2 seconds. A total of 30 words, including 10 target and 20 distracter words, is then presented, and participants are asked to choose the 10 target words immediately (Word-List Memory Task I); this is repeated for three trials. The average number of correct answers is calculated to produce a score within a range of 0–10. In addition, participants are instructed to recall (and record in writing) the 10 target words after approximately 20 minutes (Word-List Memory Task II). The total number of target words recalled is then calculated.

In the WMS-R Logical Memory subtests, two short stories (A and B) are read aloud to the participant, who is instructed to recall the details of the stories immediately (Logical Memory Task I) and after 30 minutes (Logical Memory Task II) [28]. Total scores are calculated (i.e., sum of scores for stories A and B) for WMS-R Logical Memory Tasks I and II.

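### Within-arm contrasts are given the job of showing intervention benefit, which a change over time without the control arm cannot show

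*Protocol article*

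**What the plan says.** The Statistical analyses section of the protocol article sets out three steps.

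1. The main analysis: "Between-group differences in primary outcomes subsequent to intervention will be compared using multiple linear regression analysis". Baseline score is among the covariates.
2. If the intervention effect is significant, "two planned simple contrasts will be performed to assess differences between the EI and control groups and the HI and control groups".
3. Then: "Contrasts will also be performed within each intervention group to determine whether intervention benefits are observed for the primary outcomes".

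The section closes by extending the approach: "The analysis performed for the primary outcomes will also be performed for the secondary and other outcome measures".

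Two other sections bear on step 3. Under Study population, entry requires "presence of depressive symptoms (Geriatric Depression Scale-15 [GDS-15] score of" 5 or more, together with memory problems. The memory criterion can be met by a subjective complaint or by an "age-adjusted word list memory score at least 1.0 SD below the reference threshold". Under Primary outcomes, the same two measures return: change in GDS-15, and "an improvement in memory performance, assessed via word list memory" alongside WMS-R Logical Memory. The Outcomes section schedules all measures at baseline and at two follow-ups.

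**The concern.** A contrast inside a single arm can only compare time points. The sentence gives its purpose as finding benefit, names only the two intervention groups, and does not call the contrasts descriptive or exploratory.

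Participants chosen for a high score on a scale tend to score lower when the same scale is repeated, and those chosen for a low score tend to score higher. On GDS-15 and the word list, both movements look like improvement. Repeated memory testing may add practice gains. The randomised comparison with control removes these components; a within-arm test removes none of them.

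At stake is a report in which ordinary retest change in the exercise or horticulture arm is presented as a benefit of the programme, for the primary outcomes and, through the closing sentence of the section, for the secondary and other outcomes as well.

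**Working it through.** The article gives no figure for the within-arm contrasts, so there is none to reproduce. The following illustrates how large retest change on GDS-15 could be with no treatment effect at all.

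**From the article:** entry at GDS-15 ≥ 5 (Study population); 30 per group, a target change of 1.5 points, an SD of 2.5, and non-consent and dropout of 20–30 % (Sample size). At 20 % loss, 30 × 0.8 = 24 completers.

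**Assumed, not in the article:** normal scores in the source population with mean μ = 2.5–3.5 and SD σ = 2.5; retest correlation r = 0.6–0.8; two-sided 5 % paired t-test; and, for Case A, the screening score also serving as baseline.

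**Case A: screening score used as baseline**

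- Standardised cut-off: a = (5 − μ)/σ
- Selection factor: λ = φ(a)/(1 − Φ(a))
- Expected fall: (1 − r)·σ·λ
- Variance of baseline among those enrolled: V = σ²(1 + aλ − λ²)
- SD of change: √[(1 − r)²·V + σ²(1 − r²)]

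Central example, μ = 3 and r = 0.7:

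- a = (5 − 3)/2.5 = 0.8, and λ = 1.367
- Fall = 0.3 × 2.5 × 1.367 = 1.03 points
- V = 6.25 × (1 + 0.8 × 1.367 − 1.367²) = 1.40
- SD of change = √(0.09 × 1.40 + 6.25 × 0.51) = 1.82
- Standardised change = 1.03/1.82 = 0.56; with 24 completers the test is significant in 75 % of trials

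| μ | r | Fall (points) | SD of change | Significant, n = 24 |
|---|---|---|---|---|
| 2.5 | 0.6 | 1.53 | 2.05 | 94 % |
| 2.5 | 0.8 | 0.76 | 1.52 | 66 % |
| 3.0 | 0.7 | 1.03 | 1.82 | 75 % |
| 3.5 | 0.6 | 1.22 | 2.06 | 79 % |
| 3.5 | 0.8 | 0.61 | 1.52 | 47 % |

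Over the whole grid the fall is 0.61–1.53 points, against the 1.5-point target. In simulated null trials under the same assumptions (4,000 per scenario), the within-arm test was significant in 41–90 % at n = 21 and 56–97 % at n = 30. The baseline-adjusted between-arm test stayed at 4.6–5.4 %.

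**Case B: baseline measured again after screening**

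The expected fall becomes (r_SB − r_SP)·σ·λ, where r_SB is the screening–baseline correlation and r_SP the screening–post correlation.

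- Stable true score with independent errors: r_SB = r_SP, so the expected fall is 0 and rejection is about 5 %.
- Correlation fading with time, for example μ = 3, r_SB = 0.85, r_SP = 0.65 and baseline–post 0.7: fall = 0.20 × 2.5 × 1.367 = 0.68 points, with rejection of about 40 %.

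**Practice gains:** nothing in the article allows a calculation. They are plausible because the memory tests are repeated, but their size is unknown.

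**The case against.** The strongest reply is that the main analysis is sound. The baseline-adjusted regression comes first, and nothing in the article lets a within-group result override it or defines trial success by it. That stands. The fault is confined to the inference attached to the added contrasts.

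Second, the illustration rests on choices the article does not confirm. It does not say whether the eligibility score is also the baseline score. Its SD of 2.5 refers to the study sample, whereas the model places 2.5 in the source population, which leaves an enrolled baseline SD of only about 1.1–1.3. That stands too, so the upper rates are not a forecast.

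Third, word-list selection is only one of two routes to the memory criterion, and Logical Memory is not an entry measure. Regression to the mean is therefore clearest for GDS-15 and partial for the word list.

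Two stronger readings are tempting but not supported:

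- *The within-arm contrasts are a back-up route to a positive claim after a null overall test.* The sentence carries no condition of its own, but it directly follows a conditional one and could be read as part of that follow-up. The wording is ambiguous, not an explicit second route.
- *A null between-group result beside significant within-arm change is the likely outcome.* An unadjusted two-sample t-test for 1.5 points with SD 2.5 and 24 per arm has 53 % power, but the planned model adjusts for baseline. With residual SD 2.5·√(1 − r²), power is 72 %, 81 % and 92 % at r = 0.6, 0.7 and 0.8. If the target effect is real, a null result cannot be called likely on these assumptions.

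**Conclusion.** The point holds as a fault in a stated inference. The article assigns within-arm contrasts the task of establishing benefit, and they cannot do so without the control arm. This conclusion follows from the text alone and needs none of the assumed figures.

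The size is uncertain. With no treatment effect, false significance on GDS-15 within one arm of 24 completers ranges from about 5 % (baseline re-measured, stable true score) to 47–94 % (screening score used as baseline), under the assumed source mean, SD and retest correlation. The between-group estimate and its error rate are not affected.

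**What to change.** Delete the sentence on within-group contrasts, or replace it with:

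*Within-group changes will be reported descriptively for all three groups with confidence intervals and without significance tests; conclusions about benefit rest only on the EI–control and HI–control contrasts.*

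State that the same applies to the secondary and other outcomes, since the closing sentence of the section carries the analysis over to them.

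The cost is one sentence. Data collection, sample size and the main model do not change. According to Trial status, enrolment was still open with 29 participants recruited, so the change could be made before any outcome analysis.
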